#### Mediterranean diet adherence screener (MEDAS)

2.6.8

Adherence to the Mediterranean diet will be measured using the 14-item MEDAS, developed by the PREDIMED study group.^[56]^ This scale records food consumption habits. It considers the consumption of olive oil as the main source of cooking fat, white meat and red meat, servings of vegetables, portions of fruit, red meat or sausages, animal fat, sugar-sweetened beverages, red wine, pulses, fish, commercial pastries, and dressing foods with a traditional sauces consisting of tomatoes, garlic, onions, or leeks sautéed in olive oil. The total score ranges from 0 to 14, with a higher score indicating better adherence.^[57]^

#### Insomnia severity index (ISI)

2.6.9

The ISI^[58]^ will be used to assess insomnia. This is a self-report instrument that measures a patient's perception of nocturnal and diurnal symptoms of insomnia: difficulties initiating sleep, staying asleep, early morning awakening, satisfaction with current sleep pattern, interference with daily functioning, noticeability of impairment attributed to a sleep problem, and degree of distress or concern caused by a sleep problem. This scale has 7 items, with each answer ranging from 0 to 4, and an overall score ranging from 0 to 28. The Spanish version of the ISI^[59]^ has adequate internal consistency (Cronbach alpha = 0.82).

#### Self-compassion scale (SCS)

2.6.10

The original SCS^[59]^ has 26 items that measure 6 components of self-compassion (with reverse coding of negative aspects): self-kindness, self-judgment, common humanity, isolation, mindfulness, and over-identification.^[60]^ Each item is rated on a 5-point scale that ranges from 1 (“almost never”) to 5 (“almost always”). The Spanish version of the short form of the SCS (12 items) is a valid and reliable instrument for evaluation of self-compassion in the general population.^[61]^

#### Acceptance and action questionnaire-II (AAQ-II)

2.6.11

The AAQ-II^[62]^ is a general measure of experiential avoidance and psychological inflexibility which consists of 7 statements, each of which is rated from 1 (“never true”) to 7 (“always true”). This scale measures the unwillingness to experience unwanted emotions and thoughts and the inability to be in the present moment and commit to values-directed actions when experiencing psychological events that could undermine them. The Spanish version of the AAQ-II has good internal consistency, in that Cronbach's alpha was 0.88; construct validity, in that the factor analysis led to a 1-factor solution; discriminant validity, in that the score discriminated between clinical and nonclinical samples; and external validity, in that there were strong correlations with a wide range of psychological symptoms, quality of life, and other psychological constructs.^[63]^

### Participant timeline

2.7

We will collect patient data using questionnaires administered at baseline (week-0), immediately after the intervention (week-8), at month-6, and at month-12 (Table 2).

**Table 2 T2:** Timeline for enrolment, allocation, interventions, and assessments.

	Study period				
	
	Enrolment	Intervention	Post-allocation		Close-out
				
Timepoint	−1 wk	0	8 wk	6 mo	12 mo
Enrolment					
Eligibility screen	X				
Informed consent	X				
Allocation		x			
Interventions					
MBCT intervention			x		
Lifestyles intervention			x		
Placebo		x			
Assessments					
Chronic conditions (ICD-10), BDI-II	x				
BDI-II, GCI, EQ-5D-3L			x	x	X
MOS-SS, IPAQ-SF, MEDAS, ISI			x	x	x

### Sample size

2.8

Scientific evidence suggests that a 17% reduction in the BDI-II score^[38]^ is clinically relevant.^[64]^ A previous study by our team that examined psychiatric outpatients indicated the average BDI-III score at the beginning of the study was 24.5 (SD = 9.8).^[9]^ Thus, we considered a reduction of 6 points or more to indicate a clinically significant benefit. We estimate a maximum dropout rate of 25%. Accepting an α risk of 0.05 and a β risk of 0.15 in a bilateral contrast, 60 subjects will be required for each group. Thus, the total sample size will be 180.

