One of the main challenges of Internet-based clinical interventions is the difficulty in establishing an adequate therapeutic bond, an essential component for successful psychological interventions. However, previous studies suggested that online therapies can establish satisfactory therapeutic alliances.^[30]^ Despite the great advances in the online treatment of depression, many aspects of these interventions require further study, such as the efficacy of online multimodal lifestyle programs for patients with TRD.

There is little scientific evidence supporting the benefits of an online adjuvant healthy lifestyle promotion program for patients with TRD, probably because implementation of these interventions is difficult.^[31]^ There is evidence that psychotherapy delivered by telephone or online may be useful for patients with depression, but less information is available regarding the use of Internet-based programs that focus on lifestyle in health emergency situations in which people are required to restrict their mobility and maintain physical distance.^[32,33]^ As far as we are aware, no previous studies have examined the effect of this approach for patients with TRD.

The main objective of this study is to analyze the effectiveness of treatment prescribed by the mental health team, written suggestions for lifestyle changes, and an 8-week lifestyle change promotion program in patients with TRD. There will be 2 control groups: a placebo control group will receive treatment prescribed by the mental health team and written suggestions for lifestyle changes; an active control group will receive treatment prescribed by the mental health team, written suggestions for lifestyle changes, and an 8-week iMBCT program, an intervention that has proven effectiveness in a face-to-face format.^[34,35]^

We hypothesize that patients randomized to the lifestyle intervention group will show significantly greater improvements in clinical measures of depression than patients from the 2 control groups at 12 months.

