## Discussion

3

Mental health professionals have the responsibility to adapt their health care interventions to health emergency situations, such as the current COVID-19 pandemic, and must continue to offer demonstrably useful therapeutic alternatives to their patients. Patients with TRD are among the neediest in these circumstances, because provision of face-to-face care is very difficult. This study will examine the effect of an intervention that attempts to help patients with TRD to modify their lifestyles by using information and communications technologies (ICTs) and videoconferencing instead of traditional face-to-face interactions. To assess the efficacy of lifestyle modification, we will compare this intervention group with 2 control groups: a placebo control group, which will receive minimal assistance (written recommendations for a healthy lifestyle), and an active control group, which will participate in an iMBCT program.

The time commitment is the same for the active control (iMBCT) group and the intervention (lifestyle program) group, and iMBCT has been used successfully for patients with TRD in face-to-face settings. We hypothesize that at the end of the 12-month follow-up, the lifestyle program group will show greater adherence to the intervention and will therefore experience greater improvement than the other 2 groups. If this Internet-based multimodal lifestyle intervention program is useful as an adjunct to the pharmacological treatment of depression, this approach should be considered for the management of patients with TRD in similar emergency situations.

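### The sample size gives one 6-point difference and 85% power for an unnamed contrast, so 85% power is not shown for a hypothesis that requires lifestyle to beat both controls, one of them iMBCT

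*Protocol article*

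**What the plan says.** The Introduction states the hypothesis: patients in the lifestyle arm "will show significantly greater improvements in clinical measures of depression than patients from the 2 control groups at 12 months". The Discussion repeats the expectation of greater improvement than both other groups at the end of follow-up. The two controls differ. Both receive prescribed treatment and written lifestyle suggestions; the active control adds eight 3-hour group sessions of iMBCT.

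On iMBCT, the Introduction describes the active control as "an 8-week iMBCT program, an intervention that has proven effectiveness in a face-to-face format", and the Discussion says that "iMBCT has been used successfully for patients with TRD in face-to-face settings". Both statements concern face-to-face delivery. For the online form, the Introduction says only that one recent study found it had potential.

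Section 2.8 (Sample size) begins with "Scientific evidence suggests that a 17% reduction in the BDI-II score" as clinically relevant and cites a baseline mean of 24.5 with SD 9.8. It continues: "Thus, we considered a reduction of 6 points or more to indicate a clinically significant benefit". It allows for a maximum dropout of 25% and concludes: "Accepting an α risk of 0.05 and a β risk of 0.15 in a bilateral contrast, 60 subjects will be required for each group". No contrast is named, and no separate difference is given for the comparison with iMBCT.

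**The concern.** The hypothesis has two parts and the sample size has one. Two gaps follow.

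First, power for a single pairwise contrast is not power for winning two. Even if lifestyle is 6 points better than each control, the chance that both comparisons reach significance is lower than the chance for either one.

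Second, the article does not say why 6 points should be the difference over iMBCT. The figure is introduced as a reduction beside a starting mean, so a reader cannot tell whether it is a change from baseline or a difference between arms, nor which arms. If lifestyle exceeds the placebo control by exactly 6 points, any benefit of iMBCT over that control makes the lifestyle-iMBCT difference smaller than 6.

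What is at stake is the reading of a non-significant result against iMBCT. If power for that contrast is modest, such a result would be unsurprising even when lifestyle is better, and it could be mistaken for evidence that the two programmes work equally well.

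**Working it through.** **Inputs.** From section 2.8: difference 6, SD 9.8, two-sided alpha 0.05, beta 0.15, dropout at most 25%, 60 per group. From section 2.10: 1:1:1 allocation. From the Introduction: superiority over both controls at 12 months. The article gives no expected lifestyle-iMBCT difference, so values below 6 are assumptions.

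**Step 1: reproduce the stated 60.** Two-mean formula, n = 2 × (1.960 + 1.036)² × 9.8² / 6² = 47.9, so 48 evaluable per group.
- Multiplying by 1.25 gives 48 × 1.25 = 60, the stated figure.
- Dividing by (1 − 0.25) gives 48 / 0.75 = 64, which is not the stated figure.
- A three-group ANOVA with mean differences (0, 0, 6) needs 45 evaluable per group for 85% power, and 45 / 0.75 = 60. The pattern (0, 6, 6) gives the same result.

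The stated 60 is therefore reproducible in more than one way, and the arithmetic does not reveal which contrast or pattern was intended.

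**Step 2: evaluable number.** 60 × (1 − 0.25) = 45 per group at the maximum dropout.

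**Step 3: pairwise power at 6 points.** The standard error of a difference is 9.8 × √(2/45) = 2.066, and 6 / 2.066 = 2.90. The two-sample t-test then has 82% power (83% by the normal approximation). At 48 evaluable it is 84% (85%).

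**Step 4: power to beat both controls.** The two comparisons share the lifestyle arm, so with equal groups their estimates have correlation 0.5. With a true difference of 6 against each control, each standardised margin is 2.904 − 1.960 = 0.944. The bivariate normal probability that both comparisons are significant is 0.725, about 73%. At 48 evaluable it is about 76%.

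**Step 5: smaller differences against iMBCT.** 45 per group; lifestyle 6 points better than placebo control in the last column.

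| Assumed lifestyle-iMBCT difference | Power, that contrast (t-test) | Power to beat both (normal approximation) |
|---|---|---|
| 6 | 82% | 73% |
| 5 | 67% | – |
| 4 | 48% | 46% |
| 3 | 30% | 29% |
| 2 | 16% | 16% |

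**Step 6: sensitivity.**
- Dropout: 25% is given as a maximum. With no losses at all (60 per group, normal approximation), power is 92% per contrast at 6 points and 86% to beat both. It is still only 61% at 4 points and 39% at 3 points against iMBCT.
- Baseline adjustment: at an assumed correlation of 0.5 the residual SD is 9.8 × √(1 − 0.25) = 8.49. With 45 per group, 3 points then gives about 39%.

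**The case against.** The best defence is that power is always conditional on a chosen difference, and that section 2.8 presents 6 points as a threshold of clinical benefit, not a forecast. The same threshold can apply against either control, and at 6 points each pairwise contrast has close to the stated power. That every trial loses power at smaller differences is no defect. This stands, and it rules out some stronger readings that a reader might infer:

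- *That the sizing treats both comparators as inert.* Section 2.8 names no contrast and says nothing about comparator response, and the stated 60 fits more than one pattern of means.
- *That the 85% is simply false against iMBCT.* This would need an iMBCT effect, which the article never gives.
- *That the article says online iMBCT works.* Its statements of effectiveness are confined to the face-to-face format.
- *That 17% of 24.5, about 4.2 points, can serve as the iMBCT effect.* In section 2.8 it is a relevance threshold, not an estimate for any treatment.
- *That 6 points is certainly a change from baseline.* The wording could equally mean 6 points lower than the comparator.

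It is also fair that the article plans no equivalence claim, and that ranking the contrasts may be left to a fuller document.

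The defence does not remove two things. The article does not say that 6 points is the target against iMBCT. And even if it is, at the plan's own maximum dropout the power for the two-part hypothesis is about 73%, not 85%.

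**Conclusion.** The point holds in limited form: 85% power is not shown for the hypothesis as stated. On the plan's own inputs at 25% dropout, power is about 82% for each pairwise contrast at 6 points and about 73% to beat both controls when lifestyle is 6 points better than each. This rests on SD 9.8 applying to the 12-month comparison, unadjusted tests, and success meaning significance against both controls. It depends on dropout: with no losses at all, the joint figure would be about 86%.

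For lifestyle versus iMBCT, 6 points is not justified in the text. Power would be about 67%, 48%, 30% or 16% at assumed differences of 5, 4, 3 or 2 points. These values show how sensitive the contrast is; they do not predict what iMBCT will achieve. The matter should be corrected, because section 2.8 is where a reader learns what the trial can detect.

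**What to change.** In section 2.8:

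1. State that the 6 points is a between-arm difference in 12-month BDI-II, and name the contrast or contrasts it refers to. If it is also the smallest difference of interest over iMBCT, say so and give the reason.
2. Restate power at 45 evaluable per group: about 82% for each contrast at 6 points, and about 73% to beat both controls if lifestyle is 6 points better than each.
3. Give the range for lifestyle versus iMBCT: about 82%, 67%, 48%, 30% and 16% at 6, 5, 4, 3 and 2 points, labelled as assumed differences.
4. State that a non-significant result against iMBCT is not evidence of equal effectiveness. Section 2.11 already plans 95% confidence intervals, which will show what differences remain plausible.

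Keep enrolment at 180. Whether lifestyle versus iMBCT stays confirmatory is the investigators' choice: removing it would change their hypothesis, and this point does not require that. The cost is a few sentences, with no extra patients or assessments. The downside is a less favourable stated power.

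### Section 2.8 presents the 6-point target as following from a 17% threshold and a mean of 24.5, but 17% of 24.5 is 4.2 points, so the figure used for sizing has no stated basis.

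*Protocol article*

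**What the plan says.** The sample size section (2.8) of the protocol article opens with outside evidence: "Scientific evidence suggests that a 17% reduction in the BDI-II score" is clinically relevant. It then takes a mean of 24.5 and an SD of 9.8 from the team's earlier study of psychiatric outpatients. From these two statements it concludes: "Thus, we considered a reduction of 6 points or more to indicate a clinically significant benefit". No other reason for 6 points is given.

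The error rates follow: "Accepting an α risk of 0.05 and a β risk of 0.15 in a bilateral contrast". With a maximum dropout of 25%, the result is that "60 subjects will be required for each group", 180 in all.

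The hypothesis at the end of the Introduction is comparative: the lifestyle group is to improve more than both control groups at 12 months.

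**The concern.** The linking word presents 6 points as the consequence of the two preceding figures, but those figures give a value about 30% smaller (4.2 against 6). A reader who trusts the sentence will believe the trial has 85% power for the effect that the cited evidence calls relevant. It has less, so a non-significant primary result could be reported as showing no clinically relevant benefit when an effect of the 17% size has not been excluded.

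A second ambiguity lies in the same sentence. A reduction describes change in a score. The calculation needs a difference between arms. Both control arms receive prescribed treatment and written lifestyle advice and may improve too. The Introduction describes the treatment added in the active control arm, in its in-person form, as "an intervention that has proven effectiveness in a face-to-face format". A 6-point fall in the lifestyle arm is therefore not the same as a 6-point advantage, and the section does not say which it means.

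**Working it through.** **Inputs, all from section 2.8:** threshold 17%; mean 24.5; SD 9.8; target 6 points; two-sided α = 0.05; β = 0.15; maximum dropout 25%; 60 per group.

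**1. Reproduce the stated sample size.** For two means, n = 2(z₀.₉₇₅ + z₀.₈₅)² × SD² / Δ².
- 2 × (1.960 + 1.036)² × 9.8² / 6² = 47.9, so 48 evaluable per group.
- 48 × 1.25 = 60, the stated figure.

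So 6 points is the operative target, and it is used as a between-group difference. (Inflating by 1/(1 − 0.25) would give 64. That is a separate matter, but it explains why power at 6 points falls below 85% when dropout reaches 25%.)

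**2. Check the derivation of 6 points.**
- 0.17 × 24.5 = 4.165 points.
- 6 / 24.5 = 24.5%.
- 6 / 0.17 = 35.3, the baseline mean at which 17% would equal 6 points. No such mean appears in the article.
- Standardised effects: 6 / 9.8 = 0.61; 4.165 / 9.8 = 0.425.

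**3. Power with 60 randomised per group.** Unadjusted two-sample t-test, SD 9.8, noncentrality = Δ / (SD × √(2/n)). With 25% dropout, n = 60 × 0.75 = 45.

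| Evaluable per group | Standard error | Δ = 6 | Δ = 4.165 |
|---|---|---|---|
| 45 (25% dropout) | 2.07 | ncp 2.90, power 82% | ncp 2.02, power 51% |
| 60 (no dropout) | 1.79 | ncp 3.35, power 91% | ncp 2.33, power 64% |

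**4. What a non-significant result would leave open.** With 45 per group, the 95% confidence interval has half-width 1.987 × 2.07 = 4.1 points. A non-significant observed advantage anywhere from about 0.1 to 4.1 points would have an interval that still contains 4.165.

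**5. Sensitivity to two assumptions outside the article.**
- Baseline adjustment multiplies the SD by √(1 − r²). For assumed correlations of 0.3, 0.5 and 0.7, power at 4.165 points is 55%, 63% and 80% with 45 per group, and 68%, 76% and 90% with 60.
- If the trial's own baseline mean were 30 (assumed), 17% would be 5.1 points, with 68% power at 45 per group and 81% at 60.

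**The case against.** The strongest reply is that 6 points is the criterion the authors adopted, in so many words, while the 17% is attributed to outside evidence. A trial may properly be sized on an effect larger than the smallest relevant one, and the arithmetic from 6 points to 60 per group can be reproduced. This stands: the sample size is not wrong for its chosen target. It does not rescue the sentence, which offers the 17% and the 24.5 as the grounds for 6.

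A reader might infer that the trial has only about half the power it needs for its own definition of relevance. The article does not support that as a flat statement. The 51% applies at the stated maximum dropout, without baseline adjustment, and with a baseline mean carried over from an earlier outpatient sample. With no dropout it is 64%. The statistical section names analysis of variance and does not settle whether baseline is adjusted for, and adjustment would raise the figure.

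A reader might also want to fix 4.2 points as the margin against which the confidence interval is judged. That goes too far. If the 17% refers to a patient's own reduction, 4.2 points is not a between-group margin, and such a rule would repeat the confusion described above.

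Finally, a reader might infer some particular loss of power against the mindfulness arm. The article gives no effect size for that programme and claims proven effectiveness only for in-person delivery, so no figure can be attached.

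**Conclusion.** The point holds as an error of derivation. Section 2.8 contains two thresholds, 4.2 and 6 points, joined as if one produced the other. The one that drives the sample size has no stated basis, and its nature (own change or group difference) is left open.

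The practical size is the gap between the two columns of the power table: at 4.2 points, power is 51% to 64% over the dropout range of 25% to none, against 82% to 91% at 6 points. These figures rest on SD 9.8, an unadjusted pairwise comparison at two-sided 0.05, and a baseline mean of 24.5. Baseline adjustment or a higher baseline mean would narrow the gap, but neither would make 6 points follow from the figures given.

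This should be fixed. It affects the justification and the reading of a null result; it does not affect the design, the test or the estimate.

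**What to change.** In section 2.8:
- State 6 points (d = 0.61 at SD 9.8) as the chosen between-group difference in BDI-II, with the reason for choosing it, and delete the derivation from 17%. Alternatively, keep the 17% and correct the derivation so that the figures agree.
- Say whether the 17% refers to a patient's own reduction or to a difference between groups.
- Report the power that 60 per group delivers: about 82% at 6 points with 25% dropout and 91% with none; about 51% and 64% at 4.2 points, labelled as unadjusted two-sample figures with SD 9.8.
- Add one sentence that a non-significant result does not by itself exclude an effect of the cited 17% size.

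Keep the sample size at 180. The cost is a few sentences and a less favourable power statement; no procedure changes.

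### Sample size (2.8): at the stated 25% dropout, 60 per group gives about 82% power for each lifestyle-versus-control contrast, not the stated 85%

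*Protocol article*

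**What the plan says.** Section 2.8 of the protocol article gives all the inputs. On the effect: "we considered a reduction of 6 points or more to indicate a clinically significant benefit". The only SD is 9.8, a baseline value from the team's earlier study of psychiatric outpatients. On attrition: "We estimate a maximum dropout rate of 25" per cent. The error rates and the result come together: "Accepting an α risk of 0.05 and a β risk of 0.15 in a bilateral contrast, 60 subjects will be required for each group", for a total of 180. The section gives no evaluable number before dropout, no inflation formula and no named test.

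The Introduction states the hypothesis that the design has to serve: the lifestyle group will show "significantly greater improvements in clinical measures of depression than patients from the 2 control groups at 12 months". Section 2.11 plans an analysis of variance across the three groups, with multiple imputation of missing data in the main analysis and a complete-case analysis as a sensitivity check.

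**The concern.** Section 2.8 publishes every input, so the number can be checked. For a comparison of two groups, the stated alpha, beta, difference, SD, dropout and group size do not all fit together. If 85% power is meant to survive 25% dropout, 60 per group is too few. If 60 is fixed, either the power or the dropout allowance is overstated.

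At stake is the accuracy of the figure that justifies the size of the trial. A reader who meets a non-significant contrast will judge it against a beta of 0.15, when beta at the stated dropout is nearer 0.17 to 0.18.

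**Working it through.** **Inputs** (section 2.8): difference 6 points, read as a between-group difference because the text says only that it is a reduction; SD 9.8; two-sided alpha 0.05 (z = 1.960); beta 0.15 (z = 1.036); dropout 25%; 60 per group. Allocation is 1:1:1 (section 2.10).

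**1. Evaluable patients for a pairwise contrast**

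n = 2 × (1.960 + 1.036)² × 9.8² / 6² = 47.9, so 48 per group. With the noncentral t distribution it is 49 (power 85.1% at 49, 84.3% at 48).

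**2. Reproducing the stated 60**

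| Step | Result |
|---|---|
| 48 × (1 + 0.25) | 60 |
| 48 / (1 − 0.20) | 60 |
| 48 / (1 − 0.25) | 64 |
| 49 / (1 − 0.25) | 65.3, so 66 |

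The pairwise calculation reaches 60 if the evaluable number is multiplied by 1.25, or if dropout is 20%. To keep 48 after losing 25%, the number must be divided by 0.75, which gives 64 per group, or 192 in total (t: 66 and 198).

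**3. Power at 60 randomised and 25% dropout**

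60 × 0.75 = 45 evaluable per group. The standard error of the difference is 9.8 × √(2/45) = 2.066, so the standardised difference is 6 / 2.066 = 2.904.

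- Normal approximation: Φ(2.904 − 1.960) = Φ(0.944) = 82.7%.
- Noncentral t, 88 degrees of freedom: 81.9%.

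The shortfall from 85% is 2.3 (normal) to 3.1 (t) points. The difference detectable with 85% power is (1.960 + 1.036) × 2.066 = 6.2 points (normal), or about 6.3 (t), instead of 6.

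**4. The alternative basis: an omnibus F test across three groups**

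With 45 per group and lifestyle 6 points better than two identical controls, the group means lie 4, 2 and 2 points from the grand mean. The noncentrality is 45 × (16 + 4 + 4) / 9.8² = 11.2, and power is 85.2%. At 44 per group it is 84.4%, so 45 is the minimum, and 45 / 0.75 = 60 exactly. If the active control instead lies halfway between the other two groups, the noncentrality is 45 × (9 + 0 + 9) / 9.8² = 8.4 and power falls to 73.1%.

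**5. A separate consequence: both contrasts significant**

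Suppose lifestyle is truly 6 points better than each control. The two contrasts share the lifestyle arm, so their correlation is 0.5. At 45 per group the probability that both are significant is 72.5% (bivariate normal). By simulation it is 71.3% with two-sample t tests and 71.8% with the pooled three-group variance.

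**The case against.** The strongest defence is the F test in step 4. Section 2.11 names analysis of variance, section 2.8 names no test, and an omnibus calculation with correct inflation gives 60 exactly. The word bilateral may mean no more than two-sided. So 48 × 1.25 is an inferred origin of the 60, and a reader should not take it as proven.

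This defence does not rescue the statement as printed. Section 2.8 speaks of "a β risk of 0.15 in a bilateral contrast", which fits a two-sided comparison better than a three-group test that has no direction. It nowhere assumes that the mindfulness and placebo arms have the same outcome, and the Introduction credits the mindfulness programme with proven effectiveness face to face. A significant F would not show superiority over either control, and each contrast in the hypothesis would still have about 82% power.

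A second defence is that 45 is the worst case. The 25% is a maximum; at 20% dropout, 48 remain and power is 85.1% (normal) or 84.3% (t). Multiple imputation with repeated BDI-II scores could also recover some information, and adjustment for baseline would raise power. The first part stands and limits the size of the point. The second cannot be credited: section 2.8 itself sizes for dropout as loss, and no correlation or baseline covariate is stated.

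A reader might also infer that section 2.8 promises 85% power to beat both controls and misses it by more than ten points. It makes no such promise. The joint figure of 71 to 73% follows from the hypothesis in the Introduction and from an assumed 6-point advantage over the active control as well; it is not an arithmetic error.

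**Conclusion.** The point holds for the pairwise contrast. At the stated maximum dropout, 60 per group gives about 82% power for each lifestyle-versus-control comparison (81.9% t, 82.7% normal), not 85%. The gap is 2 to 3 percentage points, or 4 patients per group (normal) to 6 (t).

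This rests on reading the 6 points as a between-group difference, on 9.8 as the SD of the analysed outcome, and on treating dropouts as contributing no information. The documents do not support calling the trial seriously underpowered: the shortfall is small, it arises only at the upper limit of expected dropout, and the SD is itself a baseline value borrowed from another sample. Minor to moderate.

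**What to change.** Keep 180 patients and restate section 2.8. Name the two-sided pairwise lifestyle-versus-control contrast of 6 points as the basis, then give one of:

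- 60 randomised per group, 45 evaluable at 25% dropout, about 82% power per contrast; or
- 60 randomised per group, 48 evaluable at 20% dropout, about 85% power per contrast (normal approximation; 84.3% with t).

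If the omnibus F test was in fact the basis, say so, state the assumption of equal controls, and still give the pairwise power.

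Add one sentence, marked as a consequence of the hypothesis, that the power to show superiority over both controls at 45 per group is about 71–72% (t) or 73% (normal) if the true advantage is 6 points over each. Quote the per-contrast and joint figures from the same method: 82% with 71–72%, or 83% with 73%.

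The cost is a few sentences and a slightly less favourable power figure. No extra patients and no change to the conduct of the trial are needed.
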